### 2.6 Safety outcomes

Safety outcomes will desaturation, hypotension, nausea or vomiting, dizziness, headache, choking cough, involuntary movement, bradycardia, and airway intervention.

### 2.7 Randomization and blinding

An independent researcher will generate random numbers using an online tool (https://www.sealedenvelope.com/simple-randomiser/v1/lists) with a 1:1:1 allocation ratio. The randomization results will be stored in sealed, opaque envelopes. Patients will be assigned to the fentanyl, nalbuphine, or placebo group. A nurse anesthesiologist not involved in other study procedures will prepare fentanyl, nalbuphine, and saline in syringes labeled only with patient numbers, which will also be marked on the outer packaging. Patients, surgeons, anesthesia providers, outcome assessors, and statisticians will all be blinded to group assignments.

### 2.8 Study interventions

In this study, patients will receive intravenous propofol combined with either fentanyl, nalbuphine, or saline during painless gastrointestinal endoscopy. Patients in the fentanyl group will receive a combination of propofol and fentanyl, those in the nalbuphine group will receive propofol and nalbuphine, and the placebo group will receive propofol with saline. All patient groups were administered 0.5 μg/kg of intravenous propofol along with either 0.03 mg of fentanyl, 3 mg of nalbuphine, or an equivalent volume of saline to induce sedation. Throughout the procedures, sedation was adjusted by titrating propofol doses, typically ranging from 0.2 to 0.3 mg/kg, to maintain the predetermined sedation level. At the start of esophagogastroduodenoscopy, the target sedation level was set at a Modified Observer’s Assessment of Alertness/Sedation (MOAA/S) scale score of 1 (responding only to trapezius squeeze stimulus). During the subsequent colonoscopy, the target sedation level was set at a score of 2 (responding only to prodding or shaking stimuli). All medications will be administered by medical professionals who are not involved in patient recruitment or data collection to maintain blinding. Randomization will be performed prior to the start of the study by an independent researcher using a computer-generated randomization table, and group assignments will be stored in sealed opaque envelopes to ensure blinding of patients, investigators, and data analysts. The study schedule for patient enrollment, interventions, and outcome assessments will follow the SPIRIT statement (Table 1). All endoscopy procedures will be performed by experienced endoscopists who have conducted at least 1,000 gastrointestinal endoscopies procedures to the study.

**TABLE 1 T1:** Schedule of patient enrolment, study interventions and outcome assessment.

Time point	Study period						
	Enrolment	Allocation	Post-allocation			Follow-up	Follow-up
	Pre-op visit	Pre-op	Intra-op	Post-op	30 min post-awake	1 week	1 month
Patient enrolment							
Eligibility criteria	×						
Written informed consent	×						
Demographic data	×						
Baseline characteristics	×						
HADS	×						
Randomization/allocation		×					
Study interventions							
Propofol + fentanyl		×					
Propofol + nalbuphine		×					
Propofol + saline		×					
Outcome assessment							
ARCI-MBG					×	×	×
ARCI-PCAG					×	×	×
ARCI-LSD					×	×	×
ARCI-Total					×	×	×
PSQI						×	×
Dream descriptions					×		
SPI			×		×	×	×
Time of induction		×			×	×	×
Time to recovery				×			×
Time awake				×			×
Endoscopists highly satisfied				×			
Patients highly satisfied				×			
Desaturation			×	×			
Hypotension			×	×			
Nausea or vomiting			×	×			
Dizziness			×	×			
Headache			×	×			
Choking cough			×				
Involuntary movement			×				
Bradycardia			×	×			
Airway intervention			×	×			
Spasm of the airway			×	×			

According to SPIRIT, statement of defining standard protocol items for clinical trials.

Pre-op, Preoperative; Intra-op, Intraoperative; Post-op, Postoperative; HADS, hospital anxiety and depression scale; ARCI, addiction research center inventory; MBG, Morphine–Benzedrine Group; PCAG, pentobarbital, Chlorpromazine, Alcohol Group; LSD, lysergic acid diethylamide; PSQI, pittsburgh sleep quality index; SPI, surgical pleth index; SPIRIT, Standard Protocol Items: Recommendations for Interventional Trials.

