**FIGURE 1 F1:**
[figure not shown]
Study flow diagram. Intervention: Three groups were administered 0.5 μg/kg of intravenous propofol along with either 0.03 mg of fentanyl, 3 mg of nalbuphine, or an equivalent volume of saline to induce sedation. Throughout the procedures, sedation was adjusted by titrating propofol doses, typically ranging from 0.2 to 0.3 mg/kg, to maintain the predetermined sedation level.

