### 2.9 Anaesthetic care

Venous access was established immediately after the patient entered the examination room, and vital signs were monitored. Intraoperative monitoring included non-invasive blood pressure (NIBP), electrocardiography (ECG), and pulse oximetry (SpO_2_). Oxygen was administered via a nasal cannula at a flow rate of 3 L/min until patients completed the gastroscopy and were fully awake. Anesthesia for the three groups of patients was induced with an intravenous injection of propofol at 1.5–2.5 mg/kg, combined with either fentanyl (0.05 mg), nalbuphine (5 mg), or an equivalent volume of saline. Sedation was adjusted throughout the procedures by titrating propofol doses, typically 0.2–0.3 mg/kg, to achieve the desired sedation level. At the start of esophagogastroduodenoscopy, the target sedation level was set at a Modified Observer’s Assessment of Alertness/Sedation (MOAA/S) scale score of 1 (responsive only to a trapezius squeeze stimulus). During the subsequent colonoscopy, the target sedation level was adjusted to a score of 2 (responsive only to prodding or shaking). Hypotension, defined as a systolic blood pressure of <80 mm Hg or a 30% decrease from baseline, and bradycardia, defined as a heart rate <45 beats/min, were treated as necessary. If SpO_2_ fell below 90% for 10 s or more, supplemental oxygen at 5–10 L/min was administered, and airway interventions, such as jaw thrust, oral or nasal airway placement, or endotracheal intubation, were performed as needed.

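### Section 2.8 and the Figure 1 legend give one set of induction doses and section 2.9 gives another, so the dose of the randomised intervention is not uniquely stated

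*Protocol article*

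**What the plan says.** Three places in the protocol article describe how sedation is induced.

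- **Section 2.8 (Study interventions):** propofol is put at 0.5 μg/kg for every group, and the rest of that sentence reads "of intravenous propofol along with either 0.03 mg of fentanyl, 3 mg of nalbuphine, or an equivalent volume of saline to induce sedation".
- **Figure 1 legend:** the same figures, "Three groups were administered 0.5 μg/kg of intravenous propofol along with either 0.03 mg of fentanyl, 3 mg of nalbuphine".
- **Section 2.9 (Anaesthetic care):** "Anesthesia for the three groups of patients was induced with an intravenous injection of propofol at 1.5–2.5 mg/kg". For the opioid or saline, the same sentence has "combined with either fentanyl (0.05 mg), nalbuphine (5 mg), or an equivalent volume of saline".

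The sections agree on what follows induction. Section 2.8 says that "sedation was adjusted by titrating propofol doses, typically ranging from 0.2 to 0.3 mg/kg", and section 2.9 describes "titrating propofol doses, typically 0.2–0.3 mg/kg, to achieve the desired sedation level". Both set the MOAA/S target at 1 for the upper endoscopy and at 2 for the colonoscopy.

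**The concern.** The opioid in the induction syringe is the only thing that randomisation varies. Its dose defines the fentanyl and nalbuphine arms, and the saline volume is specified only by reference to it. The stated aim (end of the Discussion) is to learn whether fentanyl raises, or nalbuphine lowers, euphoria after propofol. If the opioid dose is stated in two ways, neither a positive nor a null result can be tied to one regimen, and another centre could not repeat it.

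Propofol is given in all arms, so a discrepancy there does not alter the randomised contrast directly. It is nevertheless the background on which the euphoria score is measured, and the Introduction itself describes propofol as able to induce euphoria.

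The opioid conflict matters more for a second reason. Propofol is titrated to a sedation target, whereas the opioid is a fixed dose. Under section 2.7 it is drawn up by someone outside the other study procedures, in a syringe that carries only the patient number, and the anaesthesia providers are blinded. The label would not reveal a departure from the intended dose.

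**Working it through.** **Is it the same step?** Section 2.8 and the Figure 1 legend state the purpose as inducing sedation; section 2.9 states that anaesthesia was induced. All three places cover all three groups. Sections 2.8 and 2.9 then continue with the same titration range and the same MOAA/S targets. The article does not present the two sets as alternatives, as successive doses or as an amendment.

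**Inputs and ratios** (1 mg = 1,000 μg)

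| Drug | Section 2.8 and Figure 1 legend | Section 2.9 | Ratio, 2.9 to 2.8 |
|---|---|---|---|
| Fentanyl | 0.03 mg | 0.05 mg | 0.05 / 0.03 = 1.67 |
| Nalbuphine | 3 mg | 5 mg | 5 / 3 = 1.67 |
| Propofol, as printed | 0.5 μg/kg | 1,500–2,500 μg/kg | 1,500 / 0.5 = 3,000 to 2,500 / 0.5 = 5,000 |
| Propofol, if μg is read as mg | 0.5 mg/kg | 1.5–2.5 mg/kg | 1.5 / 0.5 = 3 to 2.5 / 0.5 = 5 |

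The propofol units differ by a factor of 1,000. The further factor of 3 to 5 comes from the numbers themselves.

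**Section 2.8 against itself.** The top-up of 0.2–0.3 mg/kg is 200–300 μg/kg. Against the printed induction dose this is 200 / 0.5 = 400 to 300 / 0.5 = 600, so the printed induction dose is 400 to 600 times smaller than one typical top-up.

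**Could a unit misprint explain everything?** No. With μg read as mg, propofol still differs 3- to 5-fold. The opioid doses are in the same unit in all three places and still differ by two thirds.

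**Does any computed figure depend on the doses?** The only one is the sample size in section 2.11. Its formula gives (2.396 + 0.842)² × 2 / 0.5² = 83.9, so 84 per group. Allowing for 10% dropout, 84 / 0.9 = 93.3, so 94 per group, against the stated 95. No dose enters this calculation, so the conflict leaves it unchanged.

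**The case against.** The strongest reply is that much of the intervention is defined. The sections agree on the drugs, the volume-matched saline comparator, the titration range and the sedation targets. The fentanyl-to-nalbuphine mass ratio is 1:100 in both sets (0.03 to 3 and 0.05 to 5), so the relative dosing of the two active arms is unaffected. This stands, and it confines the point to the induction doses. It does not settle the absolute opioid dose against saline.

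The large propofol ratio also depends on taking the μg symbol literally. The misfit with the top-up dose makes a unit error plausible, so both readings are shown. Neither removes the conflict.

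Finally, this is a journal article. The full protocol and the preparation instructions are not shown and may be consistent. That is fair, and it limits what can be concluded. A reader might infer that two doses are in use, that doses varied between patients, or that someone was exposed to a dosing error of several thousand-fold. The article supports none of these: it does not say which text the syringe preparer works from, and it describes titration to a sedation target. A reader might also infer that the difference between the opioid doses would change the euphoria score. The article discusses mechanisms but gives no dose-response figure, so that remains an assumption.

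Condensation for publication may excuse an omission. It does not excuse two different figures for the same step.

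**Conclusion.** The contradiction stands, as an internal inconsistency that must be corrected. The two opioid doses differ 1.67-fold, and these are the fixed doses that define two of the three randomised arms. Propofol differs 3,000- to 5,000-fold as printed, or 3- to 5-fold if μg stands for mg. The dose of the randomised intervention is therefore not uniquely stated.

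The conclusion rests only on the printed figures and on all three places describing induction, which their wording supports. It does not extend to saying that the whole intervention is undefined, that patients were dosed differently, or that the sample size is wrong. The documents do not show which set is intended, and this review does not say which figures are right.

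**What to change.** Reconcile section 2.8, section 2.9 and the Figure 1 legend against the ethics-approved protocol and the syringe-preparation instructions, so that each drug has one dose and one unit throughout.

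Recruitment was scheduled for 15 February to 31 August 2025 (section 2.1), so patients may already have been treated. If so, verify the doses actually given from the records and report them by arm. Keep the primary comparison as randomised: dose received arises after randomisation, and an unplanned adjustment for it could compromise the comparison.

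The cost is a correction in three places and a check of the preparation and dosing records. It needs no extra patients and no change to the sample size.

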### 2.9 Anaesthetic care

Venous access was established immediately after the patient entered the examination room, and vital signs were monitored. Intraoperative monitoring included non-invasive blood pressure (NIBP), electrocardiography (ECG), and pulse oximetry (SpO_2_). Oxygen was administered via a nasal cannula at a flow rate of 3 L/min until patients completed the gastroscopy and were fully awake. Anesthesia for the three groups of patients was induced with an intravenous injection of propofol at 1.5–2.5 mg/kg, combined with either fentanyl (0.05 mg), nalbuphine (5 mg), or an equivalent volume of saline. Sedation was adjusted throughout the procedures by titrating propofol doses, typically 0.2–0.3 mg/kg, to achieve the desired sedation level. At the start of esophagogastroduodenoscopy, the target sedation level was set at a Modified Observer’s Assessment of Alertness/Sedation (MOAA/S) scale score of 1 (responsive only to a trapezius squeeze stimulus). During the subsequent colonoscopy, the target sedation level was adjusted to a score of 2 (responsive only to prodding or shaking). Hypotension, defined as a systolic blood pressure of <80 mm Hg or a 30% decrease from baseline, and bradycardia, defined as a heart rate <45 beats/min, were treated as necessary. If SpO_2_ fell below 90% for 10 s or more, supplemental oxygen at 5–10 L/min was administered, and airway interventions, such as jaw thrust, oral or nasal airway placement, or endotracheal intubation, were performed as needed.

### 2.10 Data collection and monitoring

Data collection will include baseline characteristics such as age, sex, BMI, comorbidities, smoking status, alcohol consumption, education level, and scores from the Hospital Anxiety and Depression Scale (HADS), as well as the number of painless examinations. All data will be documented in case report forms (CRFs) and subsequently entered into the electronic database under the supervision of the principal investigator. An independent Data Monitoring Committee (DMC) will continuously monitor the data collection process. Once data registration is complete, the electronic database will be secured. De-identified datasets will be provided to an independent statistician for analysis based on a predefined plan. Serious adverse events (SAEs), related or unrelated to the study medication (e.g., persistent severe psychiatric symptoms), must be promptly reported to the principal investigator. The perioperative care team will take necessary actions to ensure participant safety, and these events must be reported to the DMC within 24 h for further evaluation and possible adjustments or study termination. To ensure the integrity and accuracy of the collected data, we implemented the following measures: A double-check mechanism for data entry, where all data entries are verified by a second independent researcher; Regular audits of the collected data to identify and correct any inconsistencies or errors; Standardized training for all researchers involved in data collection to ensure consistent protocols and reduce the risk of errors.

### 2.11 Sample size calculation

Based on the previous study (Li et al., 2024), the mean ARCI-MBG score 30 min after patients wake from gastrointestinal endoscopy is 8.84 with a standard deviation of 2.22. To detect a difference of 0.5 standard deviations between groups, and using the Bonferroni correction with a significance level of 0.017% and 80% power, we calculated a sample size of 95 patients per group. Considering a 10% dropout rate, the total required sample size is 285 patients, assuming a two-sided α of 0.05% and 80% power.

To calculate the sample size, we used the following formula for two independent groups with a normal distribution: n=(Z_1−α′/2_+Z_1−β_)^2^ × 2/d^2^.

Where: Z_1−α′/2_ is the critical value for a two-sided α′ of 0.017 (2.396), Z_1−β_ is the critical value for a power of 80% (0.842), d is 0.5. Using these values and applying a Bonferroni correction for multiple comparisons (α′ = 0.017).

### 2.12 Statistical analysis

The normality of continuous variables will be evaluated using the Shapiro-Wilk test. Variables following a normal distribution will be reported as mean (standard deviation), while non-normally distributed variables will be expressed as median (interquartile range). The continuous data of normal distribution were analyzed by 1-way analysis of variance, and the continuous data of nonnormal distribution among the three groups were analyzed by the Kruskal-Wallis rank-sum test. Categorical data were analyzed using the χ^2^ test or Fisher’s exact test, and the P value was adjusted according to Bonferroni method and fixed at 0.017 for pairwise comparison. P < 0.05 was considered to indicate significance.

Outcome analyses for the primary endpoint will primarily follow a modified intention-to-treat (mITT) approach, including all participants for whom relevant data are available, regardless of protocol adherence. Additionally, a per-protocol (PP) analysis will be conducted, excluding participants with protocol deviations or those who withdrew consent, to evaluate the treatment effect among those who strictly followed the study protocol. The primary outcome is the ARCI-MBG score measured 30 min post-awakening. To account for potential confounders, a covariate-adjusted linear mixed model (LMM) will be utilized. The model will incorporate fixed effects for group (treatment group), time points (30 min post-awakening, 1 week, and 1 month), and the interaction between group and time to evaluate differences across groups over time. Potential confounders, including HADS scores, sex, age, BMI, comorbidities, smoking status, alcohol consumption, education level, and the number of painless examinations, will be included as covariates in the model. Sensitivity analyses will be conducted using both mITT and PP approaches to evaluate the robustness of the findings. Additionally, these analyses will adjust for potential confounders such as sex, age, BMI, comorbidities, smoking status, and education level, to further assess the consistency of the results across different analytical methods. No interim analysis will be planned. Missing data will not be imputed. Statistical analyses will be conducted with the use of SPSS software (V.25.0; IBM SPSS).

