### 2.4 Primary outcome

The primary outcome will be the Addiction Research Center Inventory (ARCI) - Morphine–Benzedrine Group (MBG) scores, assessed via in-person interviews at 30 min post-awakening. The ARCI scale was developed by the National Institute of Mental Health Addiction Research Center (United States). The MBG, a subscale of the ARCI, measures drug-induced euphoria and helps assess whether patients experience euphoria. The MBG consists of items 1 to 16, and the sum of these items represents the euphoria score. The Chinese version used in this study was translated by experts, with its reliability and validity confirmed.

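### The primary 30-minute MBG score has two unranked analyses, and neither is tied to the pairwise mean difference that sized the trial

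*Protocol article*

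**What the plan says.** All references are to the protocol article.

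- **Endpoint.** Section 2.12 states: "The primary outcome is the ARCI-MBG score measured 30 min post-awakening". Sections 2.4 and 2.5 agree; MBG at 1 week and 1 month is secondary. Section 2.4 describes the score: "The MBG consists of items 1 to 16, and the sum of these items represents the euphoria score".
- **Sizing.** Section 2.11 takes from an earlier study that "the mean ARCI-MBG score 30 min after patients wake from gastrointestinal endoscopy is 8.84 with a standard deviation of 2.22". It sizes the trial "To detect a difference of 0.5 standard deviations between groups", using the normal two-group formula for means at a Bonferroni level of 0.017 and 80% power.
- **First analysis (2.12, first paragraph).** "The normality of continuous variables will be evaluated using the Shapiro-Wilk test". Variables that pass go to one-way ANOVA, the others to Kruskal-Wallis. The primary score is not exempted. The 0.017 pairwise level appears in the sentence on categorical data and is followed by a general threshold of 0.05.
- **Second analysis (2.12, second paragraph).** Directly after naming the primary outcome: "To account for potential confounders, a covariate-adjusted linear mixed model (LMM) will be utilized". The model has group, the three time points and "the interaction between group and time to evaluate differences across groups over time".

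Neither analysis is called primary or supportive. The Discussion says only that baseline covariates will be adjusted by suitable methods.

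**The concern.** A trial with a single primary endpoint needs one confirmatory estimate, and it should be the one the sample size was built on. Here that is the between-arm difference in mean MBG at 30 minutes, taken pairwise. Section 2.12 could be followed to the letter and still deliver something else.

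- The normality gate lets the trial's own data decide between a comparison of means and a comparison of ranks. A whole-number sum of 16 items has many ties, so the gate is likely to pick ranks even when an analysis of means would be perfectly sound.
- The mixed model contains the right contrast, but its stated purpose is differences over time. The group-by-time test asks whether the group difference changes between visits, not whether there is one at 30 minutes.

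The two routes can disagree, and the document does not say which result would be confirmatory.

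**Working it through.** **1. The plan's own sample size (2.11).** Inputs: z values 2.396 and 0.842, d = 0.5.

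n = (2.396 + 0.842)² × 2 / 0.5² = 10.4846 × 8 = 83.9, so 84 per group.

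With 10% dropout: 84 / 0.9 = 93.3, so 94. The t-based size is 85, and 85 / 0.9 = 94.4, so 95. The stated 95 per group (285 in total) is reproduced. The percent signs printed after 0.017 and 0.05 are misprints, since a literal 0.017% would need 170 per group before dropout.

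**2. Power of the contrast the trial was sized for.** 0.5 × 2.22 = 1.11 points. Two-sample t-test at two-sided 0.017: 80.1% with 85 per arm, 84.9% with 95.

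**3. How often the gate chooses ranks.** Normal scores with mean 8.84 and SD 2.22 (2.11) were rounded to whole numbers and limited to 0–16, and Shapiro-Wilk was applied at 0.05. Whole-number item scoring, the 0–16 range, the 0.05 level and underlying normality are assumptions. The document does not say whether the test is run by arm or on pooled data, so both are shown.

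| Per arm | A single arm rejects | At least one of three arms rejects | Pooled data reject |
|---|---|---|---|
| 85 | 56% | 91% | 100% |
| 95 | 66% | 96% | 100% |

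Without rounding, the pooled test rejects in 5% of trials, so ties drive the result.

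**4. What the rank test costs.** Same rounded scores, 85 per arm, one arm shifted by 0.5 SD:

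- Three-group test at 0.05: ANOVA 92%, Kruskal-Wallis 91%; same decision in about 97–98% of trials.
- Pairwise at 0.017: t-test 79%, Mann-Whitney 77%.

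The loss is 1–3 points.

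**5. What the group-by-time test detects.** Assumptions not in the document: 85 per arm with complete data, one arm shifted by 0.5 SD, equal variances, a common within-patient correlation ρ, no covariates, test at 0.05 on 4 and 3 × 84 × 2 = 504 degrees of freedom.

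- *Equal effect at all three times.* The interaction is zero by construction, so the rejection rate is the test level, about 5% (simulated 4.4–4.8%).
- *Effect at 30 minutes only.* The noncentrality is 85 × 0.25 × (2/3) × (2/3) / (1 − ρ) = 9.44 / (1 − ρ).

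| ρ | Noncentrality | Power |
|---|---|---|
| 0.2 | 11.8 | 79% |
| 0.3 | 13.5 | 85% |
| 0.6 | 23.6 | 98% |
| 0.7 | 31.5 | over 99% |

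In both scenarios the pairwise 30-minute contrast keeps its 80%, because it does not depend on what happens later.

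**The case against.** The best defence is that the first paragraph of 2.12 is generic, that the second is specific to the primary endpoint, and that the mixed model is therefore the primary analysis. The model yields the 30-minute contrast directly, and an analysis plan that is not shown may name it. This is a natural reading and may be what was intended. But the first paragraph covers all continuous variables without exception, the second states a different purpose for the model, and nothing ranks the two. The fault lies in what is written, not in missing detail.

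Several stronger readings are tempting and are not supported:

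- *That the primary endpoint itself is open.* It is not. It is fixed at 30 minutes, and the later MBG scores are already secondary.
- *That the trial is badly underpowered because a group effect averaged over three visits dilutes a 30-minute effect.* The plan never says it will test that average.
- *That the rank test seriously weakens the trial.* The loss is 1–3 points. The objection to it is the data-driven choice and the change in what is estimated.
- *That the sensitivity analyses are empty.* The article says: "Sensitivity analyses will be conducted using both mITT and PP approaches to evaluate the robustness of the findings". Comparing the two populations does probe dependence on adherence. The shorter covariate list there is introduced as examples, so it cannot be taken as complete.

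**Conclusion.** The point holds as a failure to designate the primary analysis. Two analyses cover the 30-minute MBG score, they are unranked, and neither is tied to the pairwise mean difference of 0.5 SD at two-sided 0.017 on which the 285 patients rest.

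The gate would send the score to the rank test in about 91% or more of trials if scores are normal apart from rounding; real scores could be skewed, which would also lead to rejection. The consequence for power is small; the consequence for what is estimated is not. The interaction is a reasonable test if the effect is confined to 30 minutes, and has no power beyond its 5% level if the effect is constant over time. The document does not say which pattern is expected, and the correlations of 0.2–0.7 are assumptions. The sample size is not in dispute.

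**What to change.** Amend 2.12 as follows:

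1. Name one primary analysis: the adjusted mean differences in MBG at 30 minutes between arms, from the mixed model already specified, with time as a categorical factor.
2. State that these are three pairwise contrasts, each tested at two-sided 0.017, so that the level used for sizing applies explicitly to the primary endpoint.
3. Remove the Shapiro-Wilk gate for this endpoint.
4. Label the Kruskal-Wallis or unadjusted ANOVA comparison at 30 minutes as a sensitivity analysis, and the group-by-time test as secondary.

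The cost is a few sentences, to be settled before unblinding. No extra patients or data are needed: with 85 evaluable patients per arm the named contrast has about 80% power before any gain from covariate adjustment.

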## 3 Discussion

This study is a single-center, randomized, double-blind, placebo-controlled trial involving 285 adult patients scheduled to undergo bidirectional gastrointestinal endoscopy. The primary objective is to evaluate the differential effects of intravenous propofol administration combined with fentanyl, nalbuphine, or normal saline on patient-reported euphoria during painless endoscopy. The primary outcome measure is the Morphine-Benzedrine Group (MBG) subscale score of the Addiction Research Center Inventory (ARCI), which assesses drug-induced euphoria. ARCI is a validated psychometric instrument developed by the National Institute of Mental Health Addiction Research Center, comprising MBG, PCAG, and LSD subscales that assess drug-induced euphoria, sedation, and anxiety, respectively. Specifically, the MBG subscale quantifies euphoric effects and helps determine whether patients experience significant euphoria. Secondary outcomes, including sedation and anxiety, will also be evaluated systematically at 30 min, 1 week, and 1 month after the procedure through questionnaires and ARCI scores, and related influencing factors will be analyzed statistically. This study will be conducted in accordance with the CONSORT guidelines. The trial will be conducted and reported in accordance with the Consolidated Standards of Reporting Trials (CONSORT) guidelines. To control for potential confounding effects and ensure the validity of the primary results, baseline covariates will be adjusted using appropriate statistical methods. Additionally, sensitivity analyses will be performed to assess the robustness and consistency of the findings.

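### Covariate adjustment is written only into the primary-endpoint paragraph, so on the natural reading ARCI-LSD, ARCI-PCAG, ARCI total and PSQI are compared unadjusted and may lose some precision

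*Protocol article*

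**What the plan says.** All the relevant analysis text is in section 2.12 of the protocol article.

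- The first paragraph gives the general methods. For normally distributed scores, "The continuous data of normal distribution were analyzed by 1-way analysis of variance"; otherwise "the continuous data of nonnormal distribution among the three groups were analyzed by the Kruskal-Wallis rank-sum test". No covariates are mentioned.
- The second paragraph opens "Outcome analyses for the primary endpoint will primarily follow a modified intention-to-treat (mITT) approach". It then says "The primary outcome is the ARCI-MBG score measured 30 min post-awakening", and the sentence after that is "To account for potential confounders, a covariate-adjusted linear mixed model (LMM) will be utilized". The model has group, time (30 min, 1 week, 1 month) and their interaction, with covariates "including HADS scores, sex, age, BMI, comorbidities, smoking status, alcohol consumption, education level, and the number of painless examinations".

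Section 2.10 lists the same nine variables as baseline data, and Table 1 places HADS at the pre-operative visit. Table 1 schedules no baseline ARCI or PSQI. Section 2.5 lists ARCI-PCAG, ARCI-LSD and ARCI total at 30 min, 1 week and 1 month, and PSQI at 1 week and 1 month only. The Discussion (section 3) describes the ARCI as "comprising MBG, PCAG, and LSD subscales that assess drug-induced euphoria, sedation, and anxiety, respectively", and ties baseline adjustment to the validity of the primary results.

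**The concern.** The plan collects nine baseline covariates and has already written a model that uses them. Yet it attaches that model to the euphoria score and names only unadjusted tests for the other continuous outcomes. By the protocol's own description, ARCI-LSD assesses anxiety. HADS measures anxiety and depression before the procedure, and it is the only pre-procedure psychological scale that Table 1 schedules. It is thus the nearest thing to a baseline value for ARCI-LSD, and a plausible predictor of sleep quality on the PSQI.

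At stake is the width of the intervals for the secondary outcomes. If HADS and the other covariates predict these scores, the unadjusted comparison leaves explainable between-patient variance in the error term. A chance imbalance in baseline anxiety would also go unadjusted in the anxiety comparison.

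**Working it through.** **1. Scope of the model.** Two features point to the primary endpoint: the opening of the paragraph that holds the model, and the sentence just before it, which names ARCI-MBG at 30 min. The Discussion's link between adjustment and the primary results points the same way. No sentence applies the model to ARCI-LSD, ARCI-PCAG, ARCI total or PSQI, and no sentence excludes them.

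**2. Covariate count.** HADS + sex, age, BMI, comorbidities, smoking, alcohol, education and number of painless examinations = 1 + 8 = 9. All nine are in section 2.10.

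**3. The plan's own sample size (section 2.11).** n = (2.396 + 0.842)² × 2 / 0.5² = 83.9, so 84 per group. Allowing for 10% dropout, 84 / 0.9 = 93.3, so 94 per group and 282 in total. The stated 95 and 285 are reproduced closely, as figures after dropout.

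**4. Illustrative effect of adjustment.** Inputs from section 2.11: difference d = 0.5 SD and two-sided alpha 0.017. Evaluable patients: 95 × 0.9 = 85.5, taken as 85 per group. These values were set for ARCI-MBG. The document gives no SD, target difference or power for the other outcomes, and no covariate correlation for any outcome, so the correlation ρ is an assumption.

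Adjustment multiplies the residual variance by 1 − ρ², so the effective standardized difference is d / √(1 − ρ²). Two-sample t-test power:

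| Assumed ρ | Residual variance | Effective d | Power |
|---|---|---|---|
| 0 | 1.00 | 0.500 | 80.1% |
| 0.1 | 0.99 | 0.503 | 80.6% |
| 0.2 | 0.96 | 0.510 | 81.9% |
| 0.3 | 0.91 | 0.524 | 84.2% |
| 0.4 | 0.84 | 0.546 | 87.3% |
| 0.5 | 0.75 | 0.577 | 91.1% |

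A normal approximation with 86 per group gives a similar pattern: 81.4% unadjusted and 90.0% at R² = 0.20 (ρ about 0.45).

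**5. Degrees-of-freedom cost, not included in the table.** With N = 3 × 85 = 255 and p covariate parameters, the residual variance is inflated by about (N − 4) / (N − 4 − p). Adjustment breaks even at R² = p / (N − 4).

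- Nine parameters: 9 / 251 = 0.036.
- Fifteen parameters (an assumption, if categorical covariates need several terms): 15 / 251 = 0.060.
- HADS alone, one or two parameters: 1 / 251 = 0.004 or 2 / 251 = 0.008.

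The full set therefore gives no net gain below R² of about 0.04 to 0.06. HADS alone breaks even below 0.01.

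**The case against.** The strongest objection is that the text never limits the model to ARCI-MBG. The model sentence names no outcome. Its three time points are those of every ARCI score, and MBG at 1 week and 1 month is itself secondary. The Discussion also promises some statistical analysis of influencing factors for the secondary outcomes. A condensed article that refers to a predefined plan may leave such models to that plan. This stands to the extent that exclusive use for MBG is an inference. But section 2.12 does state a method for continuous outcomes, and that method is unadjusted. The remark on influencing factors names no method and does not make the group comparison an adjusted one.

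A reader might infer that the secondary comparisons are biased. They are not: allocation is randomized 1:1:1, and the error rates of the unadjusted tests already allow for chance imbalance. A reader might also infer a known, cost-free gain. The documents do not support that either, since no correlation is given, the gain is about 2 points or less at a correlation of 0.2 or below, and the covariates use degrees of freedom. Nor do the documents show that HADS strongly predicts scores meant to capture drug-induced effects, or that it predicts sedation.

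Two practical objections stand in full. The model's 30-min time point does not fit PSQI. And relegating the rank test to description would leave no stated route for non-normal scores.

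**Conclusion.** The point holds as one of efficiency in secondary outcomes. As written, adjustment is specified only in the primary-endpoint paragraph, and on the natural reading ARCI-LSD, ARCI-PCAG, ARCI total and PSQI are compared by unadjusted tests although the covariates are at hand. The comparisons are valid. The possible loss is precision, of a size the document does not fix: from next to nothing at weak correlation to about 11 power points at an assumed correlation of 0.5, on borrowed MBG design values and before the degrees-of-freedom cost. The case is strongest for HADS with ARCI-LSD and PSQI, where the link is plausible and the cost smallest. It is weaker for the full covariate set and for ARCI-PCAG.

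**What to change.** Before unblinding, add to section 2.12 a statement that:

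- the covariate-adjusted mixed model also covers ARCI-LSD, ARCI-PCAG and ARCI total at 30 min, 1 week and 1 month, with the group contrast read at each time point;
- PSQI uses the same model with only its two time points, 1 week and 1 month;
- at minimum, if the full model is not wanted, ARCI-LSD and PSQI are adjusted for HADS;
- the rank test is kept as a sensitivity analysis for clearly non-normal scores.

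If the sponsor already intended the model to cover these outcomes, the same wording settles it. No new data, visits or patients are needed. The cost is a few degrees of freedom, some extra analysis work, and the possible loss of patients with a missing covariate, because section 2.12 rules out imputation.
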